### 9.2.3. Word Recognition Score

A speech intelligibility test is conducted at Screening (Visit 1), Day 8 (Visit 5), Day 30 (Visit 6), and Day 90 (Visit 7). Country specific test results are given as percentage or dB value of the following four items:

- Percentage of words understood in affected ear out of 40 words (at a loudness of 60 dB)
- Percentage of words understood in affected ear out of 40 words (at a loudness of 80 dB)
- Loudness (dB) with which 50 % of digits are understood in affected ear
- Loudness (dB) with which 50 % of single words are understood in affected ear.

The change in word recognition from Screening to Day 8, Day 30 and Day 90 will be analyzed for the FAS and the PPS in analogy to the primary efficacy variable separately by country, excluding the categorical analysis, the multiple linear regression, and the subgroup analyses.

#### 9.2.4. Fibrinogen Concentration

The blood coagulation parameter fibrinogen is determined at Screening (Visit 1), Day 2 (Visit 2), and Day 8 (Visit 5). Fibrinogen concentrations at Screening and Day 2 influence the duration of infusion and the dosage of study medication.

The change in fibrinogen level from Screening to Day 2 and Day 8 will be analyzed for the FAS in analogy to the primary efficacy variable, excluding the categorical analysis, the multiple linear regression, and the subgroup analyses. If a value is available twice (in the CRF and in the central lab data), both will be listed but only the CRF value will be used for statistical analysis.

#### 9.2.5. Biomarkers

The following biomarkers are determined at Screening (Visit 1) and Day 8 (Visit 5) in venous blood samples as surrogate parameters for efficacy:

- Inflammatory markers: interleukin-6, TNF- $\alpha$
- Molecular markers of leucocyte activation: CD38+, CD40+ cells.

The change in biomarkers from Screening to Day 8 will be analyzed for the FAS in analogy to the primary efficacy variable, excluding the categorical analysis, the multiple linear regression, and the subgroup analyses.

Moreover, the inflammatory and cellular markers' relative change at Visit 5 will be correlated (Spearman's correlation coefficient) with the following effects:

- PTA (Air) absolute change at Visit 5
- Fibrinogen relative change at Visit 5.

#### 9.2.6. Assessments of Hearing Impairment

During the otolaryngological examination at Screening (Visit 1), Day 8 (Visit 5), Day 30 (Visit 6), and Day 90 (Visit 7), the patients and the investigators are asked to estimate the current hearing loss by means of a numeric rating scale (NRS) with 11 items ranging from 0 to 10 points. It is understood that 0 refers to 'no hearing loss' and 10 to 'complete hearing loss'.

Separately for the patient assessment and physician assessment, the change in NRS values from Screening to Day 8, Day 30 and Day 90 will be analyzed for the FAS in analogy to the primary efficacy variable, excluding the categorical analysis, the multiple linear regression, and the subgroup analyses.

In addition, for each visit, NRS values will be transformed to three qualitative categories:

- Mild hearing loss (NRS value of 0, 1, 2, or 3)
- Moderate hearing loss (NRS value of 4, 5, or 6)
- Severe hearing loss (NRS value of 7, 8, 9, or 10).

For each visit, the absolute and relative frequency of patients within each category will be presented by treatment group. For Day 8, Day 30 and Day 50, the 3x2 contingency tables will be analyzed with the Freeman-Halton test.

#### 9.2.7. Tinnitus Severity

Tinnitus is assessed at Screening (Visit 1), Day 8 (Visit 5), Day 30 (Visit 6), and Day 90 (Visit 7). Patients rate the current tinnitus severity (ringing) by means of a numeric rating scale (NRS) with 11 items ranging from 0 to 10 points. It is understood that 0 refers to 'no tinnitus' and 10 to 'worst

tinnitus'. If the NRS is not completed and the answer 'no' to the question 'Occurrence of Tinnitus?' is provided, the NRS value 0 will be used for analysis.

The change in tinnitus severity from Screening to Day 8, Day 30 and Day 90 will be analyzed for the FAS in analogy to the primary efficacy variable, excluding the categorical analysis, the multiple linear regression, and the subgroup analyses.

### 9.2.8. Vertigo

Data on vertigo (method of nystagmography, number of spontaneous nystagmus beats per minute) are collected at Visit 1 and Visit 5 and will be presented in patient data listings.

### 9.3. Unplanned Analysis

All analyses described above are included in the study protocol with the exception of the introduction of the Per protocol set and additional subgroup analyses (use of rescue medication, isolated low and/or high frequency sensorineural hearing loss).

## 10. Safety Analyses

All safety parameters will be evaluated for all patients treated (Safety set, SFS). All statistical tables will show data by treatment group but not for overall. If not indicated otherwise, only descriptive statistics will apply.

### 10.1. Adverse Events

All adverse events (AEs) as recorded in the CRF module "Adverse Events" will be analyzed. Initially, an overview will be generated tabulating the number and percentage of patients (and the total number of events) with

- adverse events
- treatment-emergent AEs (for definition, see Section 4.3)
- treatment-emergent AEs with causal relationship (to IMP) given as 'Yes', or missing  
Note: When the answer to causality is not specified the AE will be analyzed as IMP-related
- treatment-emergent AEs leading to discontinuation ('Measures' is 'Treatment stopped')
- serious treatment-emergent AEs
- serious treatment-emergent AEs with causal relationship ('Causality' as above)
- serious treatment-emergent AEs leading to discontinuation ('Measures' as above).

For each category, AE rates of both treatment groups will be compared by Fisher's exact test.

Adverse events are coded according to the MedDRA terminology as described in the DMP. The following summaries for adverse events will be provided broken down by System Organ Class (SOC) and Preferred Term within SOC, separately for each treatment group:

- All treatment-emergent AEs (TEAEs)
- All TEAEs by maximum intensity ('Mild', 'Moderate', 'Severe', 'Life threatening', 'Death')
- All TEAEs related to IMP ('Causality' is given as 'Yes' or missing)
- All TEAEs leading to discontinuation ('Measures' is 'Treatment stopped')
- All TEAEs by action taken ('None', 'Treatment stopped', 'Dose reduced', 'Other treatment', 'Hospitalization') [1]
- All TEAEs by outcome ('Disappeared', 'Ongoing', 'Sequelae', 'Unknown', 'Death')
- All serious TEAEs

- All serious TEAEs related to IMP (causality as above)
- All serious TEAEs leading to discontinuation (measures as above).

[1] In case multiple responses per event are given, the event is counted for each response.

These summaries will generally provide the number and percentage of patients with TEAEs (and the total number of events) within each preferred term and within each SOC. Patients are counted only once for each preferred term when they have more than one AE with the same preferred term. Patients with more than one AE within a SOC will be counted for each corresponding preferred term within the SOC, but are counted only once for the SOC. The number of patients with at least one TEAE and the total number of events will also be displayed.

All tabulations will be sorted alphabetically by SOC and by frequency of preferred terms within each SOC.

A glossary of adverse events will be presented showing how investigator reported terms are actually coded to preferred terms and body systems.

All adverse events and associated collected information (including reported term, start and stop date/time, relative days and duration, treatment applied, seriousness, intensity, causality, measures taken, and outcome) will be presented by patient in a corresponding patient data listing.

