|                                |                             |               |
|--------------------------------|-----------------------------|---------------|
| Protocol Amendment 7.1         | Study no.: NM-V-101         | Page 22 of 85 |
| Date of Amendment: 15 Feb 2018 | EudraCT No.: 2012-000066-37 |               |

appears to be a safe and promising approach for the treatment of SSHL. In this double-blind, randomized, placebo-controlled parallel group proof of concept study in patients diagnosed with unilateral SSHL, ancrod has to confirm that the proposed treatment is both safe and effective if initiated within 7 days after SSHL onset.

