## 3.2 Objectives and Endpoints

The primary objective of this study is to evaluate the efficacy of ancrod as primary treatment of SSHL compared to placebo in patients with unilateral sudden sensorineural hearing loss as determined by audiometry.

The secondary objectives of this study are to:

- Evaluate the relationship between biomarkers and clinical efficacy.
- Investigate the safety and tolerability of ancrod.

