### **Safety Measures**

|                                |                             |               |
|--------------------------------|-----------------------------|---------------|
| Protocol Amendment 7.1         | Study no.: NM-V-101         | Page 59 of 85 |
| Date of Amendment: 15 Feb 2018 | EudraCT No.: 2012-000066-37 |               |

Safety data will be analyzed descriptively by treatment group. Absolute and relative frequencies will be calculated for AEs by system organ class and preferred term. The comparison of AEs between groups will be done by the exact Fisher test.

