### **10.2.2 Expected Side Effects**

Reports of bleeding AEs, as well as major bleeding, will be identified and summarized through Day 90 after initiation of study drug. Bleeding AEs will be identified using the standard MedDRA query for hemorrhages. A logistic model will be used to test for treatment group differences in the incidence of major bleeding. The logistic regression model will include terms for treatment group, age, baseline fibrinogen level, and severity of SSLH.

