## 2. Changes from Protocol including Amendments

One interim analysis after 30 evaluable patients is planned in the study protocol. As it is expected that – due to expiration of available study medication – in total only a few more evaluable patients will be enrolled than planned for the interim analysis, the interim analysis is skipped. There will only be one final analysis of study data.

The study protocol defines only the Full analysis set for analysis of efficacy but requires in addition evaluability of patients in the sample size estimation. To address this, the Per protocol set is introduced in this SAP as secondary analysis population.

The study protocol states that qualitative parameters spread in very large contingency tables will be analyzed with the asymptotic chi-square-test, but as such data do not occur this test is not used in this SAP.

According to the study protocol, demographic and pre-treatment characteristics that are continuous should be analyzed by a general linear model (GLM) to determine comparability of the ancrod and placebo groups at baseline. If treatment group differences were seen at the 0.10 level of significance, these variables would be added as stratification variables or covariates to the efficacy analyses. As the study is randomized, it was decided to not follow this request and to not assess baseline differences.

The study protocol leaves open whether an analysis of covariance or a general linear model should be used to evaluate the primary efficacy variable and quantitative secondary efficacy variables. As the primary efficacy variable (change from Baseline) may be dependent on the baseline value, the baseline value should be taken into account for the primary analysis as covariate. For this reason, statistical evaluation will be performed using a generalized linear model, without prior investigation at the BDRM.

Introduced by several protocol amendments, various changes have been implemented in the CRF. However, the statistical analysis of patients being included in the study prior to an implemented CRF change is not affected, and values will be missing for added CRF parameters for all patients enrolled under a previous protocol amendment; a footnote for the respective summary tables will clarify the data issues referring to CRF amendments. In detail, the following changes relevant for the statistical analysis were made to the CRF:

- Exclusion criterion 17 was added with Amendment 4.1

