| Display of ranges                                                    | xx – yy                                                                                                                                                                                                                                                                                                                                                                                                                                                                                                       |
| Display of 2-sided confidence intervals                              | [lower limit ; upper limit]                                                                                                                                                                                                                                                                                                                                                                                                                                                                                   |
| Display of units                                                     | Presentation case-sensitive and in round brackets, e.g. '(kg)'                                                                                                                                                                                                                                                                                                                                                                                                                                                |

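### The AE comparison in SAP 10.1 rests on Fisher p-values alone; without an interval beside them, a non-significant result at the likely sample size says little about safety

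*Combined protocol and SAP*

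**What the plan says.** **Objective.** Protocol 3.2 lists as a secondary objective: "Investigate the safety and tolerability of ancrod". The rationale in Protocol 2.2 is worded more strongly: "ancrod has to confirm that the proposed treatment is both safe and effective if initiated within 7 days after SSHL onset".

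**Method for adverse events.** Protocol 10.2.1 (Safety Measures) says: "The comparison of AEs between groups will be done by the exact Fisher test". SAP 10.1 applies this to seven overview rows: any AE; treatment-emergent AEs; related ones; those leading to discontinuation; serious ones; serious and related; and serious leading to discontinuation. The wording is "For each category, AE rates of both treatment groups will be compared by Fisher's exact test". For other safety output, SAP 10 sets the default: "If not indicated otherwise, only descriptive statistics will apply".

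**Intervals.** None is attached to a safety outcome. The line "Display of 2-sided confidence intervals" in SAP 13.4 is a formatting rule, and the safety tables listed in SAP 13.2 name no interval.

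**Bleeding.** Protocol 10.2.2 adds a summary of bleeding events by a standard MedDRA query and a model: "A logistic model will be used to test for treatment group differences in the incidence of major bleeding". The SAP contains neither, and its list of changes in SAP 2 does not record dropping them.

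**Size.** Enrolment of 99 was planned (66 ancrod, 33 placebo; SAP 3.5). SAP 2 now expects that "in total only a few more evaluable patients will be enrolled than planned for the interim analysis", that interim analysis having been set at 30 evaluable patients.

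**The concern.** A p-value from a test of no difference answers one question: whether the data are incompatible with equal rates. In a trial of some 30 patients it will often be non-significant even when the true rates differ a good deal. Seven non-significant p-values in the AE overview table can then be read as no difference in adverse events. Ancrod lowers fibrinogen, and Protocol 2.4.1 acknowledges a bleeding risk.

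An interval would not make the trial more sensitive. It would show what size of excess the data cannot exclude, which is the information a small phase II safety table can honestly give. SAP 2 already adapts to the smaller size by cancelling the interim analysis, but the safety comparison was left unchanged.

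**Working it through.** **1. The plan's own figure.** The stated sample size concerns efficacy only: difference 15 dB, SD 20 dB, two-sided 5%, power 90%, 2:1.

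Placebo n = (1 + 1/2) × (1.960 + 1.282)² × 20²/15² = 1.5 × 10.51 × 1.778 = 28.02, rounded up to 29. Ancrod 58, total 87. With 12% dropout (SAP 5.3), 87/0.88 = 98.9, so 99.

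The figure reproduces. No rate, margin or power is stated for any safety outcome.

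**2. Assumptions for the safety check.**
- Final size: 30 to 39 patients at 2:1, that is 20:10, 22:11, 24:12 or 26:13. This is an assumed reading of SAP 2, which gives no number.
- True AE rates: assumed, since the documents give none.
- Test: two-sided Fisher at 5%.

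**3. Probability of missing a true excess.** For each size, find every pair (x ancrod events, y placebo events) with Fisher p ≤ 0.05, sum the product of the two binomial probabilities over those pairs, and subtract from 1.

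| True rate, ancrod v placebo | 20:10 | 22:11 | 24:12 | 26:13 | 66:33 (planned) |
|---|---|---|---|---|---|
| 20% v 5% | 98% | 97% | 95% | 93% | 53% |
| 30% v 10% | 90% | 88% | 85% | 81% | 40% |
| 60% v 40% | 89% | 88% | 86% | 83% | 60% |
| 30% v 5% | 85% | 80% | 74% | 68% | 12% |
| 40% v 10% | 70% | 68% | 61% | 55% | 10% |

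The first three rows, excesses of 15 to 20 points, span about 81 to 98% at 30 to 39 patients. The last two rows, 25 and 30 points, are missed clearly less often.

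**4. Events needed when placebo has none.** At each of the four sizes the smallest ancrod count with p<0.05 is 8: 8/20 = 40%, 8/22 = 36%, 8/24 = 33%, 8/26 = 31%. At 22:11, 7 events give p=0.067 and 8 give p=0.031.

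**5. What an interval adds.** The Newcombe interval combines the Wilson limits (l, u) of the two rates. With d = p1 − p2:
- lower = d − √[(p1 − l1)² + (u2 − p2)²]
- upper = d + √[(u1 − p1)² + (p2 − l2)²]

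For 7/22 v 0/11: p1 = 0.318 with Wilson limits 0.164 and 0.527; p2 = 0 with limits 0 and 0.259.
- Lower: 0.318 − √(0.155² + 0.259²) = 0.017
- Upper: 0.318 + 0.209 = 0.527

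So the difference is +32 points, 95% interval +2 to +53, beside a Fisher p of 0.067.

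For 0/22 v 0/11: p=1.0, but the interval still reaches +15 points.

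**6. Upper limit with zero ancrod events.** One-sided 95% Clopper-Pearson limit = 1 − 0.05^(1/n). At n=22 this is 12.7%; across 20 to 26 ancrod patients it runs from 13.9% to 10.9%.

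**The case against.** The strongest reply is that this is exploratory output from a phase II proof-of-concept trial. SAP 5.6 confines confirmatory testing to the primary efficacy variable. SAP 10.1 already gives counts and percentages by arm, breaks events down by organ class, preferred term and intensity, and lists each event by patient. A reader of 7/22 v 0/11 sees 32% v 0% without any p-value. All of that stands, and it makes this an improvement in reporting, not a flaw that invalidates the trial. It does not remove the gap: percentages alone do not show their uncertainty, and exploratory analyses are where estimates with intervals serve better than tests.

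Four stronger readings are tempting, and the documents do not support them.
- *The trial formally undertakes to confirm safety.* The wording in Protocol 2.2 is background prose. The objective is to investigate.
- *Fisher is the only between-arm safety inference planned.* That is true of the SAP but not of both documents, because Protocol 10.2.2 prescribes a logistic model for major bleeding.
- *Most clinically relevant harms will be missed.* No document defines a relevant harm. The miss rates apply to one comparison at assumed rates and size, and they fall as the excess grows.
- *The plan treats p>0.05 as proof of safety.* No passage says so.

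Nor does 7/22 v 0/11 establish harm. Fisher's test is conservative in small samples and the Newcombe interval is approximate, so the two can fall on different sides of the 5% line.

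**Conclusion.** The point holds as a cheap and worthwhile improvement. The SAP's only between-arm inference on adverse events is a set of Fisher p-values, with no effect estimate, interval or bound. If the trial ends with 30 to 39 patients at 2:1, an excess of 15 to 20 points is missed in about 81 to 98% of trials under the three rate pairs examined; 40% v 10% is missed in 55 to 70%. A non-significant p-value would therefore say little about safety, whereas an interval would show how large an excess remains possible.

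The size is inferred from SAP 2 and the rates are assumed. The Safety Set takes in treated patients with any post-dose safety information (SAP 4.1), so it may be somewhat larger than the evaluable count, which would lower the miss rates a little. At the planned 66:33 the problem is smaller but still present: 40 to 60% for the same three pairs.

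The absence from the SAP of the bleeding analyses in Protocol 10.2.2 is a related but separate discrepancy. Intervals on the seven overview rows would not resolve it.

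**What to change.** In SAP 10.1 and Table 14.3.1.1:
- Beside the Fisher p-value for each of the seven categories, add the risk difference (ancrod minus placebo) with a two-sided 95% Newcombe interval.
- Where ancrod has zero events, add the one-sided 95% Clopper-Pearson upper limit of the ancrod rate (12.7% at 0/22).
- State that a non-significant p-value is not evidence of no difference. Set no pass-fail rule on the upper limits, because the documents define no safety margin.

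Keeping the Fisher test preserves consistency with Protocol 10.2.1. The cost is an added column in one table and a few lines of SAP text, with no new data or patients, and it can be settled before unblinding. The downside is a safety statement that looks less certain.

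Separately, reconcile Protocol 10.2.2 with the SAP: either carry the bleeding summary and the logistic model into SAP 10, or record and justify their omission in SAP 2.

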## 10.2. Death and Other Serious Adverse Events

In addition to the general AE listing, a separate patient listing will be generated for serious adverse events and death cases. Summary tables on serious TEAEs are described in Section 10.1.

## 10.3. Laboratory Data

Data on laboratory parameters are provided in the CRF or electronically by the central lab. They refer to blood coagulation, clinical chemistry, hematology, biomarkers, antibodies, and urinalysis; relevant for safety purposes are all except biomarkers. If a value is available twice (in the CRF and in the central lab data), both will be listed but only the CRF value will be used for statistical analysis.

All results of laboratory tests will be listed, including reference ranges (available only for central lab data) and possible details on conversion to the standardized units shown in below table. Unusual lab values are reviewed at the BDRM. Values recorded as lower or upper border only will be evaluated as the border (e.g. >140 as 140); however, if all values of a parameter are recorded as border value, the analysis will only be categorical.

The laboratory parameters will be displayed in the analysis in the order as shown in Table 2:

TABLE 2: LABORATORY PARAMETERS

| Group      | Parameter (standardized unit)        |
|------------|--------------------------------------|
| Hematology | Hemoglobin (g/dL)                    |
|            | Hematocrit (%)                       |
|            | Erythrocytes ( $10^6/\mu\text{L}$ )  |
|            | Leukocytes ( $10^3/\mu\text{L}$ )    |
|            | Thrombocytes ( $10^3/\mu\text{L}$ )  |
|            | Mean cell volume ( $\mu\text{m}^3$ ) |

| Group           | Parameter (standardized unit)         |
|-----------------|---------------------------------------|
|                 | ESR (mm/h)                            |
| Blood chemistry | Creatinine (μmol/L)                   |
|                 | GOT/ASAT (U/L)                        |
|                 | GPT/ALAT (U/L)                        |
|                 | Sodium (mmol/L)                       |
|                 | Potassium (mmol/L)                    |
|                 | Chloride (mmol/L)                     |
|                 | Glucose (mmol/L)                      |
|                 | Urea (mmol/L)                         |
|                 | Uric acid (μmol/L)                    |
|                 | Phosphorus (mmol/L)                   |
|                 | Total bilirubin (μmol/L)              |
|                 | Total protein (g/L)                   |
|                 | Albumin (g/L)                         |
|                 | LDH (U/L)                             |
|                 | GGT (U/L)                             |
|                 | Alkaline phosphatase (U/L)            |
|                 | Creatinine phosphokinase (μkat/L)     |
|                 | Triglycerides (mmol/L)                |
|                 | Cholesterol (mmol/L)                  |
|                 | HDL (mmol/L)                          |
|                 | LDL (mmol/L)                          |
|                 | VLDL (mmol/L)                         |
| Coagulation #   | Thrombin time (sec)                   |
|                 | Prothrombin time (INR)                |
|                 | aPTT (sec)                            |
| Urinalysis      | Hemoglobin or blood in urine * °      |
|                 | pH (no unit)                          |
|                 | Specific gravity (no unit)            |
|                 | Protein (mg/L)                        |
|                 | Glucose (mmol/L)                      |
|                 | Ketones *                             |
|                 | Bilirubin *                           |
|                 | Leukocytes *                          |
| Antibodies      | Neutralizing anti-ancrod antibodies * |

